### Analyses

#### Statistical analyses of effectiveness

Analysis will be by intention to treat, in that all available data will be included. Methods of imputation such as LOCF (last observation carried forward) are of limited utility in dementia, where the expectation is decline for the usual treatment group, and participants will be lost through death and illness. Hence our sample size calculations are based on the numbers estimated to be available at the study end-point, 6 months after randomisation to either the CST only group or the maintenance CST group. Multi-level modelling will be used to address the issue of clustering within randomised groups. We shall also use analysis of covariance to adjust for baseline differences in outcome variables [37]. Analyses will consider the evaluation 6 months after the second randomisation as the primary end-point. Secondary analyses will consider the effects immediately following the CST, at 3 and 6 months. Age, gender, cholinesterase inhibitor and baseline scores on the scales being examined will be entered as covariates, together with 'centre' entered as a random factor, because treatment has been defined as participation in the group programme within the confines of the centres.

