## Methods/Design

The design is a single-blind, multi-centre, randomized controlled trial of Cognitive Stimulation Therapy (CST) groups for dementia vs. Maintenance CST groups (extra 24 sessions once a week) (Figure 1). After completion of the initial CST programme (twice weekly, 45-minute sessions for 7 weeks), participants are randomly allocated into treatment group (maintenance sessions once a week for 24 weeks) or control group (treatment as usual for 24 weeks).

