### Randomisation

The randomisation process in this trial is undertaken in two stages, randomisation 1 and randomisation 2. Figure 1 sets out the two-stage randomisation process. The allocation ratio at randomisation 1 stage is 1:1; into either group A or group B, with both groups receiving 7 weeks of CST. The allocation ratio at randomisation 2 stage is 1:1; into either the control group or treatment group. The sample is stratified to ensure that equal numbers of participants taking cholinesterase inhibitors are randomised into either the Maintenance CST or the control group. The North Wales Organisation for Randomised Trials in Health (NWORTH) is responsible for undertaking the remote randomisation. NWORTH is accredited as a Clinical Trials Unit by the UK Clinical Research Collaboration (UKCRC) and funded as part of the Clinical Research Collaboration Cymru, notably for HTA trials.

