### Blinding

Although participants cannot be blinded to their allocated treatment, all follow-up data is gathered by interviewers blind to groups. However our experience in the CST trial, as shared by similar projects, is that participants may occasionally and inadvertently inform researchers of the treatment they are receiving. We aim to reduce this effect by giving explicit reminders to participants before the assessment visit and by the use of self-report measures wherever feasible. Assessors record their impression of which arm of the trial each participant belongs to and their confidence in that prediction on completion of the two follow up assessments. This enables us to test whether inadvertent loss of blinding leads to bias, and to adjust for any bias that may be detected.

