### Outcome measures

Primary and secondary measures are completed at baseline (T0), after the seven weeks of the CST programme (first follow up, T1), three months after beginning of the maintenance groups (second follow-up T2) and six months after the beginning of the maintenance groups (third follow up and primary end-point T3).

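### The covariate called baseline reads as the pre-CST score (T0), although T1 is the natural pre-randomisation assessment, and the plan lists an effect at T1, where no randomised contrast exists

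*Protocol article*

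**What the plan says.** All places are in the protocol article.

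- **Methods/Design**, on when the arms are formed: "After completion of the initial CST programme (twice weekly, 45-minute sessions for 7 weeks), participants are randomly allocated into treatment group" or control.
- **Randomisation**, first stage: participants go "into either group A or group B, with both groups receiving 7 weeks of CST". Second stage: "The allocation ratio at randomisation 2 stage is 1:1; into either the control group or treatment group".
- **Outcome measures**, on the visit labels: "Primary and secondary measures are completed at baseline (T0), after the seven weeks of the CST programme (first follow up, T1"). T2 and T3 are timed at three and six months from the start of the maintenance groups and are numbered second and third follow-up.
- **Statistical analyses of effectiveness**, on the primary time point: "Analyses will consider the evaluation 6 months after the second randomisation as the primary end-point". On covariates: "Age, gender, cholinesterase inhibitor and baseline scores on the scales being examined will be entered as covariates". On secondary analyses: "Secondary analyses will consider the effects immediately following the CST, at 3 and 6 months".
- **Sample Size** counts the required 230 participants at T1.
- **Blinding** has assessors record their guess of the arm and their "confidence in that prediction on completion of the two follow up assessments".

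**The concern.** The question the trial asks, maintenance CST against usual care after CST, is created by randomisation 2. The best-placed pre-randomisation score is normally the one nearest to that allocation, here T1. The plan's labels point elsewhere: the score called baseline was taken before a seven-week active treatment, and the nearer score is classed as an outcome.

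Two things are at stake. First, the primary model for both primary outcomes may use the weaker of two scores already collected. Since two scores could be called baseline, the choice should also be fixed before data are seen. Second, an effect at T1 is listed in the same sentence as the randomised comparisons at 3 and 6 months. A reader of the results could then take a T1 finding as evidence of a treatment effect that the design cannot estimate.

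**Working it through.** **Order of events.** Methods/Design puts the maintenance-or-control allocation after the CST course. Outcome measures puts T1 after the same seven weeks and times T2 and T3 from the start of the maintenance groups. Sample Size counts participants at T1. Together these support the order T0, CST, T1, randomisation 2, T2, T3. No sentence says outright that T1 is completed before allocation, and Figure 1 is not shown.

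**Which score is meant by baseline.** The analysis section does not write T0. Outcome measures attaches the word to T0, and the cost item under Secondary Outcomes also separates baseline from the assessment after treatment. In addition, the analysis section plans an analysis at T1, and a T1 score cannot be the baseline for itself. T0 is the literal reading.

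**What exists at T1.** Randomisation 1 creates groups A and B, which receive the same CST. Randomisation 2 comes after CST. So at T1:
- a difference between the later arms has expected value zero by design;
- a T0–T1 change has no control group and mixes any CST effect with practice effects, regression to the mean and decline.

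**Effect on precision.** The plan states no figure here to reproduce, and the documents give no correlations, so every correlation below is an assumption. Let a = corr(T0,T3), b = corr(T1,T3), c = corr(T0,T1). As a fraction of the outcome variance, the residual variance is
- T0 only: 1 − a²
- T1 only: 1 − b²
- both: 1 − (a² + b² − 2abc)/(1 − c²)

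With c = 0.75, so 1 − c² = 0.4375:

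| a, b | T0 only | T1 only | both |
|---|---|---|---|
| 0.60, 0.70 | 1 − 0.36 = 0.640 | 1 − 0.49 = 0.510 | 1 − 0.22/0.4375 = 0.497 |
| 0.60, 0.60 | 0.640 | 0.640 | 1 − 0.18/0.4375 = 0.589 |
| 0.80, 0.70 | 1 − 0.64 = 0.360 | 0.510 | 1 − 0.29/0.4375 = 0.337 |

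In the first row T0 leaves 0.640/0.510 = 1.25 times the residual variance left by T1. In the second, T1 alone gains nothing. In the third, T1 alone is worse (0.510/0.360 = 1.42). In every row, using both is at least as good as the better single score.

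If a is allowed to run from 0.60 to 0.80 and b from 0.70 to 0.85 independently, T1 alone gives anything from 57% lower residual variance (a = 0.60, b = 0.85: 0.2775/0.64 = 0.43) to 42% higher (a = 0.80, b = 0.70).

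**What this means for power.** Taking 230 with 15% attrition gives 230 × 0.85 = 195.5 analysed, or 97.75 per arm. For a standardised effect of 0.39, two-sided 5% and clustering ignored, power = Φ(0.39/√(2v/97.75) − 1.96), where v is the residual variance:
- unadjusted, v = 1: 77.8%
- T0, v = 0.64: 92.6%
- T1, v = 0.51: 96.8%

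The smallest effect detectable with 80% power is 0.32 SD with T0 and 0.29 SD with T1.

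**Bias.** A simulation with the first-row correlations (5,000 runs, 98 per arm, true effect 0.39) gave a mean estimate of 0.389 with either covariate. The SD of the estimate was 0.112 with T0 and 0.100 with T1.

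**The case against.** The strongest reply is that nothing here invalidates the primary analysis. T0 also precedes randomisation 2, cannot be affected by allocation, and gives an unbiased adjusted estimate. That stands. A reader might infer that the plan's covariate biases the result; the documents do not support that, and the simulation shows no bias. Chance imbalance at T1 is not a second harm either: it is already in the standard error of the T0-adjusted estimate, so it is the same loss of precision seen another way.

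A second reply is that T1's advantage is not established. This also stands. The Background reports that gains from a related intervention had faded one month or 10 weeks after stopping, so a score taken straight after CST could carry a transient gain. A reader might want one percentage for the loss, but the assumed ranges reach from a large gain to a loss with T1 alone. Even in the favourable example, the difference is a few points of power above 90%.

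Third, the analysis section never writes T0, and it times the end-point from the second randomisation. That leaves some room to read baseline as T1. The literal reading is still T0, and an ambiguity in the primary covariate needs the same repair.

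Fourth, a reader might take the two follow-ups in Blinding as proof that T1 precedes allocation. That section does not name T2 and T3. It is consistent with that order, but it also conflicts with the three follow-ups numbered in Outcome measures.

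Fifth, the T1 analysis is secondary and specifies no between-arm test, so a pre-post description may be all that is meant. That is possible, but the sentence calls it an effect and lists it with the randomised comparisons, so it needs a different label.

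**Conclusion.** The point holds as a moderate one with two parts.

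1. The baseline covariate reads as T0, while T1 is the natural pre-randomisation assessment. T0 adjustment is valid and unbiased, but probably less precise, because T1 is nearer the end-point and reflects individual response to CST. The illustration of 0.64 against 0.51 rests on assumed correlations of 0.60 and 0.70; the gain from T1 alone vanishes if the two are equal and reverses if T0 predicts better. Entering both scores avoids having to know which case applies.
2. The analysis listed immediately after CST cannot estimate a treatment effect, because neither randomisation has produced a treatment contrast by then. This follows from the design and needs no numerical assumption.

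The order of T1 and randomisation 2 is inferred from several sections that agree, without the flow diagram. The documents do not support saying that the primary estimate is biased or that its conclusion is in danger.

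**What to change.** - **Statistical analyses of effectiveness:** name the T1 score of the scale being analysed as the baseline covariate for the T2 and T3 comparisons, and keep its T0 score as a second covariate. Precision is then essentially never lost, the only price being one extra model parameter.
- **Same section:** restrict treatment-effect analyses to T2 and T3. Report T0–T1 change only as an uncontrolled description of the CST phase, without a test of effect.
- **Outcome measures:** relabel T1 as the assessment before randomisation 2, and state that it is completed before allocation is disclosed, if that is so.
- **Blinding and Outcome measures:** reconcile the two follow-ups in the one with the three in the other.

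The cost is wording only. Both scores are already collected, and neither the visits nor the sample size change. The edits should be made before any analysis by arm.

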### Participants

Recruitment to this trial is currently taking place through day centres, residential homes and Community Mental Health Teams (CMHTs) in the participating study centres, with at least a minimum of 14 potential participants. Half of the sample to be recruited from the community (50%) and the other half of the sample (50%) from care homes. Potential centres (day centres, CMHTs and residential homes) are screened for eligibility to determine whether there are sufficient numbers of potential participants with dementia, using the inclusion criteria flow chart. (Appendix 1). People with dementia meeting the inclusion criteria are recruited into the two CST groups that are running per centre (7 to 10 per group).

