#### Sample Size

The primary outcome measures are cognition (ADAS-Cog) and quality of life (QoL-AD) at 24 weeks follow up. In the pilot CST trial [6] which recruited people with mild/moderate dementia (MMSE 10-24), community and institutional participants had a similar level of cognitive impairment (mean MMSE 14.5 and 14.1). The RO review [5] found a moderate effect size of 0.58 between the RO and control groups though the studies had some differences in methodology, outcome measures, and length of treatment/follow up. The MCST pilot study found a large effect size of 1.0 compared with CST alone. To detect an effect size for MCST of 0.39 on the ADASCog with power of 80% using a 5% significance level and an estimated attrition of 15% needed, a sample size of 230 at T1 is required. If an estimated 60 participants will have Alzheimer's disease and are suitable/willing to take cholinesterase inhibitors (ACHEIs), this provides sufficient numbers for the maintenance CST/ACHEIs trial platform to estimate effect size and the feasibility of the trial.

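### The only random factor named is centre, which may not carry therapy-group clustering, and the sample size of 230 makes no allowance for that clustering

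*Protocol article*

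**What the plan says.** The Statistical analyses of effectiveness section makes two statements about dependence. The first is general: "Multi-level modelling will be used to address the issue of clustering within randomised groups". The second comes in the sentence listing the covariates and names the only random factor in the article, with a reason: "together with 'centre' entered as a random factor, because treatment has been defined as participation in the group programme within the confines of the centres".

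The Participants section says that people are "recruited into the two CST groups that are running per centre (7 to 10 per group"). The opening of Methods/Design says participants are allocated after the 7-week programme to weekly maintenance sessions or to usual treatment, and the Randomisation section gives a 1:1 ratio at that stage. Each maintenance group has two facilitators and runs for 24 sessions.

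The Sample Size section gives its inputs as "To detect an effect size for MCST of 0.39 on the ADASCog with power of 80% using a 5% significance level", and then "an estimated attrition of 15% needed, a sample size of 230 at T1 is required". It states no ICC, cluster size or design effect.

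**The concern.** The reason given for the centre factor shows that it is meant to stand for the group programme. Whether it can do so depends on the layout. If a centre contributes both maintenance participants and controls, a centre intercept is common to both and drops out of the within-centre comparison of arms. What remains is the dependence from meeting weekly in one maintenance group with the same members and facilitators. That is present among a centre's maintenance participants and absent among its controls, so a shared intercept cannot represent it.

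Two things are at stake. If the model has no group level, the intervals for both primary outcomes could be too narrow. And the stated 80% power makes no allowance for a feature that the analysis section itself says has to be handled.

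**Working it through.** **Inputs from the article.** Standardised difference 0.39, power 80%, significance level 5% (two-sided assumed), attrition 15%, 230 at T1, 1:1 allocation, 7 to 10 per CST group, two groups per centre.

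**Assumptions.** ICC of 0.02 to 0.10 (none is given); maintenance groups the same size as CST groups; one maintenance group per centre; clustering in the maintenance arm only.

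**1. The plan's own figure.** n per arm = 2 × (1.960 + 0.842)² / 0.39² = 103.2, so 104 per arm and 208 analysed. Allowing for 15% attrition gives 208 / 0.85 = 245, or 208 × 1.15 = 240 by the cruder rule. Neither is 230, so the figure leaves no slack that might be a tacit clustering allowance.

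**2. Power before clustering.** 230 × 0.85 = 195.5 analysed, or 97.75 per arm. SE = √(2 / 97.75) = 0.1430. Power = Φ(0.39 / 0.1430 − 1.960) = 77.8%.

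**3. Power with clustering in the maintenance arm.** With m analysed per group, D = 1 + (m − 1) × ICC, SE = √[(D + 1) / 97.75], and power = Φ(0.39 / SE − 1.960). Here m runs from 7 × 0.85 = 5.95 to 10 × 0.85 = 8.5.

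| ICC | D | Power | N at T1 for 80% power |
|---|---|---|---|
| 0.02 | 1.099 to 1.150 | 75.8% to 74.8% | 255 to 262 |
| 0.05 | 1.248 to 1.375 | 73.0% to 70.6% | 273 to 289 |
| 0.10 | 1.495 to 1.750 | 68.5% to 64.3% | 303 to 334 |

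The N column includes the attrition shortfall from step 1.

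**4. Detectable difference at ICC 0.05.** 2.802 × √(2.248 / 97.75) = 0.425 and 2.802 × √(2.375 / 97.75) = 0.437, so about 0.42 to 0.44. Without clustering it is 2.802 × √(2 / 97.75) = 0.40.

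**5. Type I error if centre is the only random level.** Two simulations, each with both arms in every centre and clustering in the maintenance arm only:

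| ICC | 14 centres, 7 per arm per centre, 20,000 trials | 13 centres, 15 per centre, centre variance 0.03, 4,000 trials | Mean model SE / true SE (second simulation) |
|---|---|---|---|
| 0 | not run | 5.4% | 0.995 |
| 0.02 | 5.8% | 5.9% | 0.965 |
| 0.05 | 6.9% | 7.9% | 0.913 |
| 0.10 | 9.2% | 9.0% | 0.864 |

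The second simulation used a normal critical value and starts from 5.4%, so a little of its excess is not due to clustering. In the first, adding the group level brought the error back to 4.8-5.2%.

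**6. Number of centres.** 230 / 20 = 11.5 and 230 / 14 = 16.4, so about 12 to 17.

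**The case against.** - **The group level may be intended.** The multi-level sentence can be read as promising one, and nothing says centre is the only level. A reader might infer that the planned standard error is certainly too small; the article does not support that. What stands is a mismatch between a general promise and the one random factor named with its reason.
- **Detail may sit in an analysis plan that is not shown.** The full random structure and the degrees-of-freedom method properly belong there. The named factor, its rationale and the sample size are in the article and can be judged from it.
- **Both arms in each centre is an inference.** Two groups per centre and 1:1 allocation make it likely, but no text says the second randomisation is within centre, and the flow diagram is not available. Step 5 depends on it.
- **Clustering in both arms would look worse.** At ICC 0.05, power would be 64-69% and type I error 9.0%. That needs groups as the randomised unit, or carry-over from the 7-week groups. The article describes allocating participants, so those figures are not relied on here.
- **Not all the power loss is clustering.** About 2 points come from the attrition arithmetic. From 77.8%, one-arm clustering costs about 5 to 7 points at ICC 0.05 and 2 to 3 at 0.02.
- **The Abstract speaks of comparing 230.** If 230 were all analysed, power would be 84.1% without clustering and 77.5% at ICC 0.05 with 8.5 per group. The Sample Size section, however, places 230 at T1, before the attrition.
- **Baseline adjustment may recover the loss.** Adjustment for the baseline score is planned. Multiplying the variance by 1 − r² with the residual ICC unchanged, 80% power at ICC 0.05 needs r² = 1 − (0.39 / 0.425)² to 1 − (0.39 / 0.437)², so r of about 0.40 to 0.45. The article gives no correlation and claims no such gain, so a definite loss of 80% power is not shown, but neither is its attainment.

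**Conclusion.** The point holds in conditional form. The sample size makes no allowance for therapy-group clustering, and on its own inputs 230 gives 77.8% power before any. With clustering in the maintenance arm, unadjusted power is about 75-76%, 71-73% or 64-69% at ICC 0.02, 0.05 or 0.10.

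The standard error is too small only if three things hold together: each centre supplies both arms, centre is the only random level fitted, and the group ICC is above zero. Type I error is then about 6%, 7-8% or 9% at the same ICCs. At 0.02 or below the effect is minor. The ICC is an assumption throughout. The change is worth making because it affects both primary outcomes and is largely a matter of wording.

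**What to change.** In the Statistical analyses of effectiveness section, reconcile the two sentences. Keep centre and name a random effect for therapy group: partially nested in the maintenance arm if participants are the unit of the second randomisation, or group within centre if groups are. State which applies and whether that randomisation is within centre. Specify a small-sample degrees-of-freedom correction such as Kenward-Roger, since only about 12 to 17 centres are implied.

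In the Sample Size section, state an assumed ICC and group size, and restate the power or the detectable difference on the numbers left after attrition (about 0.42-0.44 at ICC 0.05 with one arm clustered). If baseline adjustment is relied on to recover power, give the assumed correlation and show the gain.

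The cost is revised wording, somewhat wider intervals and a less favourable stated figure. No extra participants are needed.

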#### Economic evaluation

The primary economic evaluation is a cost-effectiveness analysis. This study also offers an opportunity to conduct a secondary cost-utility analysis. In addition, all costs and effects for people with dementia will be set out in a cost-consequence analysis. This analysis takes a public sector perspective spanning the NHS (dementia services, primary and secondary care) and social care services funded or brokered by local authorities. The interventions received will be fully costed from the perspective of local dementia services to generate a total programme cost and cost per participant. We will estimate costs from data collected in the validated Client Service Receipt Inventory (CSRI), completed with the family care-giver or care home manager. Costs will include those associated with the CST and maintenance CST groups, primary and secondary health care services used by participants in the intervention and control arms of the study (e.g. home/surgery telephone contacts with GP and practice nurse, outpatient and inpatient attendances at secondary care, prescribing), home care, residential care placements, care and support accessed through direct payments (or personal budgets), as well as indirect costs associated with caregiver time and lost productivity.

